### Study groups and randomization process

Consecutive patients on the waiting/referral list for PSVT ablations (referred to our tertiary center by other hospitals) will be screened for eligibility by dedicated study coordinators. When they meet the inclusion criteria, the patients will be enrolled in the study (as depicted in the flowchart for the study; see Fig. 1). After enrolment, patients will be allocated a unique study subject number in chronologically ascending order. Subsequently, they will be randomized to two treatment arms: the “CF-sensing” arm, ablation with a CF-sensing ablation catheter; and the “conventional” arm, standard ablation approach using a conventional (noncontact force-sensing) ablation catheter. Randomization will be performed by a computer-generated program (ALEA) based on a block randomization protocol using a block size factor of four. Randomization into the two treatment arms will be carried out with a 1:1 randomization ratio (50% probability for both treatment arms). The process of randomization will follow the general concepts of allocation concealment by incorporating the following prerequisites into the conduct of randomization: the EP specialists performing the ablation procedures do not have knowledge on the method of randomization utilized in the study; the EP specialists performing the ablation procedures do not keep a record of the results of randomization during previous ablation procedures; withdrawal from enrolment and randomization after the initial screening process and the subsequent EP study (that was positive for AVNRT or WPW-AVRT) must be explained thoroughly in the official clinical report by the treating specialist; the person in charge of the randomization process will not be the treating physician and neither will he/she be involved in the patient selection process; and the person in charge of the randomization will be contacted (over the telephone) by the treating specialist after the diagnostic part of the procedure has been completed. Stratification for study specific factors will not be conducted. The study will be performed in an open-label fashion: neither the patient nor the electrophysiologist (performing the procedure) will be blinded for the specific type of procedure.

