### Statistical analysis

The number of radiofrequency applications during the ablation procedures of AVNRT and WPW-AVRT (primary study endpoints), as well as other continuous procedural parameters from the group of secondary study endpoints (such as total procedural duration, fluoroscopy time and overall duration of RF applications), will be expressed as mean ± SD or median (interquartile range) depending on their distributions, and statistical analysis of these variables will be conducted using either the two-sample *t* test or the Mann–Whitney test, again depending on the underlying distribution of the data.

The recurrence rate of PSVT at 1 year (as an indicator of long-term success rate of the index procedure), as well as the acute success rate and the major/minor complication rates of the index procedures (secondary study endpoints), will be presented as absolute and relative frequencies. The associations between treatment and these secondary endpoints will be analyzed with the chi-squared test or with Fischer’s exact test, as appropriate. Moreover, logistic regression will be performed to examine these associations and will, if needed, be adjusted for unbalanced baseline characteristics. Freedom from PSVT recurrence will be determined with Kaplan–Meier analysis, and differences in recurrence-free survival rates will be evaluated with the log-rank test. A *p* value of 0.05 will be considered significant for all statistical determinations, and all reported *p*-values will be based on two-sided tests.

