### Sample size calculation

The sample size calculations were based on the following:
A retrospective analysis of AVNRT/WPW-AVRT ablations performed in our institute within the last 6 months revealed that the mean number of radiofrequency applications required for successful ablations was 4.81 ± 3.21, which is in line with previous results found in the literature [30].According to previous studies, the ablation efficiency for patients with atrial fibrillation has been increased with the use of CF-sensing technology by approximately 15–20% [1, 4–19], as revealed by the reduced number and duration of RF applications in atrial fibrillation ablation. We assume that in terms of ablation efficiency, the significance of CF sensing will be even more pronounced in the treatment (catheter ablation) of such simple arrhythmia substrates as that of AVNRT and WPW-AVRT, therefore (regarding our sample calculations) a 25% reduction in RF application number was considered realistic to represent a clinically significant change.

Evaluation of the distribution of RF applications in our database of AVNRT/WPW-AVRT ablations (mentioned under the first point) revealed a positive skewness, and therefore logarithm transformation (natural log) was performed in order to approximate a normal distribution of the variables. The mean and standard deviation of the natural logs of application numbers were computed and amounted to 1.39 ± 0.59; these values were subsequently used in our sample size calculations.

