For the sample size calculations, we used two different calculator tools: an online sample-size calculator tool (http://powerandsamplesize.com/Calculators/Compare-2-Means/2-Sample-Equality) and G*power (http://www.gpower.hhu.de/en.html). In both methods, we applied the appropriate test comparing the difference of two independent means of two groups (calculation formulas are presented on the calculator’s website and in G*power). The mean application number of the group with the study catheter was assumed to be reduced by 25% (as already mentioned) compared to the control group (thus amounting to 1.39 × 0.75 = 1.043) and the standard deviation of this group was assumed to be identical to the control group. The power was set to 80% and the type 1 error (α) to 5% (two-tailed). Using these parameters, both methods/calculators determined the same sample size of patients (2 × 46 = 92), which would be required to show a statistical significance in the case of a clinically significant reduction (25%, as mentioned earlier) of RF application number.

Allowing a dropout rate of 15%, the total sample size would become around 106. In addition, the acute success rate of AVNRT/WPW-AVRT ablations has been reported to be around 95% [26, 29]. Taking this into consideration, the total number of patients required for the purposes of this study would be 112.

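### The primary test is left to the observed distribution and ignores AVNRT versus WPW-AVRT, which is known before randomisation; one prespecified log-scale model adjusted for mechanism would be sharper and leave less discretion

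*Protocol article*

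**What the plan says.** All references are to the protocol article.

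- **Primary analysis (Statistical analysis).** RF application number is compared by a two-sample t test or a Mann–Whitney test, the choice "again depending on the underlying distribution of the data". No criterion for the choice is given and no covariate is named.
- **Distribution known at design (Sample size calculation).** The centre's own counts were positively skewed, so a "logarithm transformation (natural log) was performed in order to approximate a normal distribution of the variables". The log values "amounted to 1.39 ± 0.59". The CF-sensing arm was set at 75% of that log mean ("thus amounting to 1.39 × 0.75 = 1.043"), giving 46 per arm with both diagnoses pooled.
- **Mechanism known before allocation (Study population; Study groups and randomization process).** AVNRT or WPW-AVRT must be identified at the EP study for a patient to be eligible. The person in charge of randomisation is "contacted (over the telephone) by the treating specialist after the diagnostic part of the procedure has been completed". Nevertheless, "Stratification for study specific factors will not be conducted". The trial is open-label.
- **Binary secondary endpoints (Statistical analysis).** Besides chi-squared or exact tests, logistic regression is planned and "will, if needed, be adjusted for unbalanced baseline characteristics".

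**The concern.** The skew and the log-scale behaviour of the endpoint were known when the plan was written, so nothing about the distribution needed to wait for trial data. The comparison that the sample size refers to, a difference in log means, is not among the permitted analyses. Since the trial is open-label and the selection criterion is not stated, the person who picks the test may already know how each candidate turns out.

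The two diagnoses are different ablation targets. The Background gives acute success of 96–97% versus 93% and recurrence of about 5% versus 8%. If they also differ in RF count, that explainable variation stays in the error term of an unadjusted test, although the factor is recorded for every patient before allocation.

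For the binary secondary endpoints, letting observed imbalance decide the covariates leaves the model open until the data are seen. Few recurrences will be available to support it.

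**Working it through.** **1. The plan's own figure.** Inputs from Sample size calculation: log mean 1.39, SD 0.59, difference 1.39 × 0.25 = 0.3475, two-sided α 0.05, power 80%.

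n per arm = 2 × (1.960 + 0.842)² × 0.59² / 0.3475² = 45.3, so 46 per arm and 92 in total. This reproduces the stated figure. Power at 46 per arm is 80.6% by the normal approximation and 79.8% by the noncentral t.

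**2. What the permitted tests deliver.** Simulated trials of 46 per arm used lognormal counts (log mean 1.39, SD 0.59), rounded to whole numbers with a minimum of 1. The effect was the planned 0.3475 or zero. There were 8,000 trials per scenario.

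| Analysis | Type I error | Power at 0.3475 |
|---|---|---|
| Raw-scale t test | 4.9% | 72.8% |
| Mann–Whitney | 4.7% | 77.0% |
| t test on log counts (not planned) | 4.8% | 78.4% |
| Rule: t test if Shapiro–Wilk p > 0.05 in both arms, otherwise Mann–Whitney | 4.75% | 77.0% |
| Smaller of the t and Mann–Whitney p-values | 6.9% | not a valid test |

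A repeat with 20,000 trials gave power of 72.9%, 77.2% and 78.8% for the first three rows and 7.05% type I error for the smaller p-value. The rounded figures are therefore 73%, 77%, 79% and 7%. The Shapiro–Wilk rule is an assumed way of making the plan's wording operational. It selected the t test in 2 of 8,000 null trials and in none under the planned effect.

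**3. What adjustment for mechanism could add.** The article gives neither the case mix nor RF counts by diagnosis, so R², the share of log variance explained by mechanism, is an assumption. Residual SD = 0.59 × √(1 − R²). Power is by the noncentral t at 46 per arm with a difference of 0.3475. The last column is the ratio of geometric-mean counts between diagnoses that each R² implies at an assumed 60% AVNRT share: exp(0.59 × √(R² / (0.6 × 0.4))).

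| R² (assumed) | Residual SD | Power | Implied ratio |
|---|---|---|---|
| 0 | 0.590 | 80% | 1.00 |
| 0.02 | 0.584 | 81% | 1.19 |
| 0.10 | 0.560 | 84% | 1.46 |
| 0.20 | 0.528 | 88% | 1.71 |
| 0.30 | 0.494 | 92% | 1.93 |

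**4. Chance imbalance in case mix.** With a proportion p of one diagnosis, the between-arm difference in its share has SD √(2p(1 − p)/46). That is 9.6 points at p = 0.3 and 10.4 points at p = 0.5. Differences of this size are ordinary without stratification, and adjustment removes their contribution to the estimate.

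**5. Events available for the logistic models.** At recurrence of 5% to 8% (Background) and 112 patients, 112 × 0.05 = 5.6 and 112 × 0.08 = 9.0, so about 6 to 9 recurrences in total.

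**The case against.** The strongest reply is that little is lost. The plan ties the choice to the distribution, not to the result. With counts as skewed as the centre's own, a formal check leads almost always to Mann–Whitney, which is unaffected by a log transformation and trails the log-scale t test by only 1 to 2 points. Type I error under such a rule stays at the nominal level. This stands. The 73% for the raw t test belongs to a branch that a formal check would rarely reach, and the 7% arises only if someone selects on the p-value, which the plan does not invite. It remains true that no criterion is stated, so the text does not rule these routes out.

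Second, the gain from adjustment has no source in the article. This also stands. The larger gains need counts that differ between diagnoses by about 1.5-fold to 1.9-fold, and at R² of 0.02 the gain is about one point.

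Third, the normality criterion and the covariate list usually sit in a statistical analysis plan, which is not shown. That would answer a complaint about missing detail. Here the article itself states the rules: a test chosen from the data and covariates chosen by imbalance.

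A reader might infer more than the documents support:

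- **That the analysis is invalid or biased.** It is not. Chance imbalance is already reflected in the unadjusted standard error.
- **That the trial is short of power because it is unadjusted.** At its planned difference, the unadjusted log-scale power is about 80%. Lower figures appear if the true effect is taken as ln 0.75 = −0.288, but that is a separate question about how the 25% reduction was scaled.
- **That the imbalance rule governs the primary endpoint.** It is stated only for the binary secondary endpoints.
- **That separate primary comparisons by diagnosis are intended.** The plural wording about primary endpoints might suggest it, but the sample size covers one pooled comparison.

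**Conclusion.** The point holds as one of precision and prespecification. The primary test should not wait for the trial's distribution when the skew was known and the trial was sized on logs. A baseline factor fixed before allocation should not go unused.

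Moving from Mann–Whitney to a log-scale analysis is worth about 2 points of power, and from the raw t test about 6 points. Adjustment for mechanism adds between about 1 and 12 points, depending on an R² that the article does not give. Naming a single analysis also closes the route to a type I error of about 7%.

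The test comparison assumes lognormal counts with the stated log mean and SD and the planned difference of 0.3475. For the binary secondary endpoints the harm is an open choice of covariates with about 6 to 9 recurrences. It was not quantified further.

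**What to change.** In Statistical analysis:

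1. Replace the data-dependent choice with one primary analysis: a linear model of ln(number of RF applications) with treatment and mechanism (AVNRT or WPW-AVRT), reported as an adjusted ratio of geometric means with 95% CI.
2. State in advance how a zero count is handled. The logarithm is undefined there, and the exclusion rules do not clearly remove a patient whose study catheter was introduced but who received no RF application.
3. Keep a Mann–Whitney test stratified by mechanism (van Elteren) as a sensitivity analysis only, so that the primary estimate and p-value come from the same model.
4. For the binary secondary endpoints, delete the conditional adjustment for imbalance. Fix mechanism as the single covariate and use a penalised (Firth) logistic model because few events are expected.

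The cost is a short protocol amendment, made before analysis; the Ethics section says that inclusion was still ongoing. No new data are needed, since mechanism is established for every eligible patient. The randomisation need not be changed to stratify, because adjustment gives the main benefit.

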### Electrophysiology procedure and catheter ablation

#### Preprocedural preparation and electrophysiology (EP) study

The procedures are performed under local anesthesia. In the case of a patient on anticoagulation therapy, this is decreased/discontinued before the procedure according to local guidelines. Antiarrhythmic medication is stopped 5 days before the procedure. The diagnostic EP study is implemented according to standard protocols for diagnosing SVTs: vascular access is created with femoral venous puncture and multipolar diagnostic catheters are placed in standard locations within the cardiac chambers: the coronary sinus, the right ventricle and the region of the bundle of His. Intravenous heparin is used during the procedure for anticoagulation (guided by the activated clotting time when necessary). Standard pacing maneuvers (atrial/ventricular extrastimulus testing, atrial/ventricular incremental pacing and specific pacing maneuvers to assess accessory pathway conduction and to induce and analyze SVTs) are performed to confirm the diagnosis of AVNRT or WPW-AVRT. After confirming the diagnosis of AVNRT/WPW-AVRT, the operator informs the patients about the specific diagnosis and briefly describes the expected success rates and safety concerns regarding the ablation of the particular subtype of arrhythmia substrate. Next, in order to continue with ablation, verbal consent is obtained from the patient (see protocol flowchart in Fig. 1).

#### Mapping and ablation of the underlying arrhythmia substrate

In the case of a left-sided ablation, the choice of access to the left atrium/ventricle (retrograde via the femoral artery vs. a transseptal approach) is left to the discretion of the operator. Transseptal punctures are guided by intracardiac echocardiography (ICE).

Depending on the results of the randomization, the subsequent steps of mapping/ablation are performed using either a conventional (nonirrigated, non-CF-sensing) manual RF ablation catheter (conventional arm) or the TactiCath Quartz open-irrigated contact force-sensing catheter (CF-sensing arm). Stable catheter–tissue contact (minimum of 10 s in duration) with a minimum CF exceeding 5–10 g (and an optimal CF within the range of 15–20 g) is targeted in the CF-sensing group. The TactiCath catheter is used in a virtual “nonirrigated mode” (saline flow set to ~ 1 ml/min) to achieve a similar degree of temperature control as in the case of conventional nonirrigated catheters. In both groups, the power (usually between 15 and 55 W) and the duration (usually between 60 and 90 s) settings of individual RF applications will follow local laboratory standards and will be left at the operator’s discretion. The ablation procedures are continued until the clinical tachycardia is no longer inducible and/or the conduction through an accessory pathway is terminated, provided that these clinical endpoints can be achieved with acceptable clinical risk–benefit ratios (e.g. no signs of imminent complete AV-block, no signs of pericardial effusion, etc.). Thereafter, the inducibility of the clinical tachycardia and/or conduction over an accessory pathway is reassessed throughout a waiting time of 30 min from the last RF application. No additional applications are implemented until further programmed stimulation shows evidence for recurrence of inducibility and/or re-conduction over an accessory pathway.

#### Exclusion of enrolled patients from further follow-up

Patients who were originally enrolled into the study (registered in the database and randomized to one of the two treatment arms) are excluded from further follow-up in the case of the following scenarios:
The ablation catheter is not introduced into the patient due to prior occurrence of a serious AE (note: not during the ablation process itself), to the withdrawal of consent or to any type of technical difficulty with the setup.The ablation catheter is not introduced into the patient or ablation is discontinued before the achievement of acute success due to a clinical decision to utilize a different type of catheter that is not compatible with the study design (e.g. magnetic-navigation guided catheters, cryoablation catheters, etc.). Such clinical scenarios include, for example, parahisian accessory pathways (switching to cryoablation to prevent AV node injury), ablation of epicardial accessory pathways from a coronary sinus branch (magnetic navigation guided catheter for better access) or any other situation where the specific anatomy of the underlying arrhythmia-substrate involves an increased potential risk thereby necessitating the utilization of special approaches.

However, those individuals for whom ablation was implemented with a “study-compatible” ablation catheter yet the applications were prematurely discontinued due to the occurrence of (serious) AEs will indeed be taken into consideration for further analyses (i.e. these patients will not be excluded from further follow-up) in order to be able to assess the safety aspects of CF sensing vs*.* non-CF sensing during catheter ablation.

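### Randomised patients switched to a non-study catheter before acute success leave follow-up, and apparently analysis, on the decision of an unblinded operator

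*Protocol article*

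**What the plan says.** The rule is in the protocol article, section 'Exclusion of enrolled patients from further follow-up'. It applies after allocation, to patients "registered in the database and randomized to one of the two treatment arms) are excluded from further follow-up". Two of its triggers matter here.

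- The allocated catheter is never introduced, for reasons that include an earlier serious adverse event, withdrawal of consent "or to any type of technical difficulty with the setup".
- The catheter is not introduced, or "ablation is discontinued before the achievement of acute success due to a clinical decision to utilize a different type of catheter", where that other catheter does not fit the study design. The examples are anatomical (parahisian and epicardial pathways), but the list closes with "or any other situation where the specific anatomy of the underlying arrhythmia-substrate involves an increased potential risk".

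The next paragraph makes one exception. Patients whose applications with a study catheter were stopped early because of adverse events "will indeed be taken into consideration for further analyses (i.e. these patients will not be excluded from further follow-up".

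The section 'Study groups and randomization process' places the randomisation call after the diagnostic part of the procedure and says that "neither the patient nor the electrophysiologist (performing the procedure) will be blinded for the specific type of procedure". Under 'Primary and secondary outcome parameters', the number of RF applications is primary; acute success or failure, adverse events and long-term success are among the secondary outcomes. The section 'Statistical analysis' names no analysis set.

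**The concern.** A patient who starts ablation with the allocated catheter, has not reached acute success and is moved to another technology has, for that strategy, an unsuccessful result. The rule takes this patient out after randomisation, on a judgement made by someone who knows the arm. Setup difficulty can also differ by arm, because only one arm uses a contact-force system.

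If such exits are more frequent in one arm, or come from different kinds of case in the two arms, the remaining groups are no longer the groups that were randomised. Acute success is affected most directly, because the rule conditions on success not having been reached. Recurrence at 12 months and later adverse events are affected next, because nobody collects them in these patients. The RF count is affected if the patients who leave are those who would have needed unusually many, or unusually few, applications.

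**Working it through.** **1. Does the text link follow-up to analysis?** The exception for adverse-event stops is phrased as being kept for analysis, and explained by an 'i.e.' as not being excluded from follow-up. The natural converse is that patients who are excluded from follow-up are not analysed. The section 'Sample size calculation' also enlarges the total for a 95% acute success rate, which hints that acute failures were not expected to contribute to the primary comparison. Neither passage defines an analysis set.

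**2. The plan's own numbers.** Inputs from 'Sample size calculation': log mean 1.39, SD 0.59, difference 1.39 × 0.25 = 0.3475, two-sided 5%, power 80%.

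- n per arm = 2 × (1.96 + 0.84)² × 0.59² / 0.3475² ≈ 45.3, so 46 per arm and 92 in total.
- 92 × 1.15 = 105.8, so 106.
- 106 / 0.95 = 111.6, so 112, or 56 per arm.

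The stated 92, 106 and 112 reproduce.

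**3. Acute success.** Assume 5% failures without a switch in both arms, and a share s of switches in the contact-force arm only. With everyone kept, success in that arm is 1 − 0.05 − s. After exclusion it is (1 − 0.05 − s)/(1 − s).

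| s | All randomised, control vs CF | After exclusion, control vs CF |
|---|---|---|
| 5% | 95% vs 90% | 95.0% vs 94.7% |
| 10% | 95% vs 85% | 95.0% vs 94.4% |

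With 10% switching in both arms there is no false difference, but each arm reports 94.4% where the all-randomised figure is 85%.

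**4. RF count, worst case.** Suppose there is no true effect, log counts are N(1.39, 0.59) in both arms, and the highest share f is lost from one arm only. The log mean of that arm shifts by −0.59 × φ(c)/(1 − f), where c is the (1 − f) normal quantile.

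- f = 5%: −0.59 × 0.1031/0.95 = −0.064, ratio of geometric means 0.94.
- f = 10%: −0.59 × 0.1755/0.90 = −0.115, ratio 0.89.
- f = 15%: −0.59 × 0.2332/0.85 = −0.162, ratio 0.85.

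Simulated trials with 56 per arm and a two-sample t test on the log counts give these two-sided type I errors:

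| What is lost | 5% | 10% | 15% |
|---|---|---|---|
| Highest counts, one arm | about 10% | about 20% | about 30% |
| Random patients within the top third, one arm | about 6% | about 10% | about 17% |
| Highest counts, both arms equally | 7–9% across the range, ratio 1.00 | | |
| Random patients, one arm | about 5%, ratio 1.00 | | |

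**5. Would counting applications up to the switch cure it?** No. Assume no true effect, and that 5%, 10% or 15% of one arm switch after a single application. If that single application is scored as a completed count, type I error is about 8%, 20% and somewhat over 30%. An early switch is then credited as a good result. A patient in whom the catheter was never introduced would score zero, which has no logarithm.

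**The case against.** The strongest reply is that the section concerns follow-up and defines no analysis set. RF counts and acute results are known by the end of the procedure, so a separate analysis plan could keep them. This stands in part: a reader might infer that the protocol orders removal from analysis, but it only implies it. The reply does not reach recurrence and later adverse events, because data that are never collected cannot be restored.

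Second, a reader might infer that treatment failures in general disappear. They do not. The rule covers switches to catheters that do not fit the design, and its examples are anatomical. Acute failures without such a switch are not removed by it, and adverse-event stops are kept. The open-ended last clause is what makes the rule wider than its examples.

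Third, nothing in the document says that switchers have the highest RF counts. A switch made because of anatomical risk may come early, and some patients never receive a study application. The 10%, 20% and 30% figures assume both one-arm loss and loss of exactly the top counts.

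Fourth, one might read the 15% dropout allowance as a budget for these exclusions. The document does not say what it covers, so that reading is a guess, and the point does not rest on it.

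Last, the safety loss is limited. Adverse events during the procedure and before discharge are still assessed; what goes missing is later follow-up of switchers.

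**Conclusion.** The point holds and should be corrected. The protocol states a post-randomisation exclusion from follow-up that an open-label operator triggers, that turns on acute success not having been reached, and that has no closed list of reasons. Loss of 3- and 12-month recurrence and adverse-event data in these patients is certain under the rule. Loss from analysis is the likely reading but is not stated.

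The size cannot be estimated, because the document gives no switch rate overall or by arm. Under the assumptions shown, a 10-point difference in acute success could shrink to 0.6 points (95.0% vs 94.4%). Type I error for the RF count lies between about 5% (random loss) and about 30% (worst case at 15% one-arm loss). The upper figures are a bound under stated assumptions and should not be read as the error rate of this trial. Equal switching in both arms would leave little bias in the difference but would still overstate success in each arm.

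**What to change.** 1. Keep every randomised patient in the allocated arm for analysis. Unless consent is withdrawn, keep them in the scheduled 3- and 12-month visits for recurrence and adverse events.
2. Count a switch to a non-study catheter before acute success as acute procedural failure.
3. For the primary endpoint, do not treat the applications up to the switch as a completed low count. One workable choice is the worst rank for switchers in the Mann–Whitney comparison that 'Statistical analysis' already foresees, with the raw count to the switch reported alongside and sensitivity to other handling shown. State in advance how patients without any study application are handled.
4. Where the diagnostic EP study already shows that a non-study catheter will be used, record this and exclude the patient before the randomisation call. This catches only part of the cases, because mapping with the allocated catheter comes after randomisation.
5. Keep the current set as a per-protocol sensitivity analysis.

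Operators' freedom to switch is unchanged. On the plan's own assumptions no extra recruitment is needed, since 112 randomised exceeds the 92 required. The cost is a wording change, already scheduled visits for a few more patients and slightly lower reported success rates. The worst-rank analysis also makes the primary result a combination of RF count and switching, which the report must say.
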